#### Analysis

Final analysis of the primary and secondary outcome measures will be carried out at study closure defined as the date of database lock. The principle of intention to treat analysis will be performed blind to treatment allocation.

Longitudinal data will be analysed using mixed models with survival outcomes analysed using Kaplan-Meier curves with log-rank tests and Cox Proportional Hazard models. The potential for jointly modelling longitudinal data with survival outcomes will be explored[50]. The use of these regression models will allow us to consider the relationships between thyroid status and factors that could modulate the effect of thyroid supplementation. A separate statistical analysis plan will be developed prior to the internal pilot.

A secondary per protocol analysis will also be considered.

## Adverse Event Reporting and Safety Evaluations

### Definitions

#### Adverse event (AE)

Any untoward medical occurrence in a subject recruited to a clinical trial, including occurrences which are not necessarily caused by or related with the treatment. An adverse event can be any unfavourable and unintended sign or symptom associated with the use of a medicinal product whether or not related to that product.

#### Adverse reaction (AR)

Any untoward and unintended response in a subject to an investigational medicinal product which is related to any dose administered to that subject.

#### Serious adverse event (SAE), serious adverse reaction (SAR) or unexpected serious adverse reaction

Any adverse event, adverse reaction or unexpected adverse reaction, respectively, that

a) results in death,

b) is life-threatening,

c) requires hospitalisation or prolongation of existing hospitalisation,

d) results in persistent or significant disability or incapacity, or

e) consists of a congenital anomaly or birth defect.

### Expected Serious Adverse Events

Extremely premature babies below 28 weeks' gestation constitute a high risk population: the following are serious adverse events and incidence rates which could be reasonably expected for this group of babies during the course of the study (Table 1).

**Table 1 T1:** List of Expected Serious Adverse events

Adverse event	Estimated incidence
a) death	20%*
b) necrotising enterocolitis or focal intestinal perforation diagnosed on clinical grounds, or at surgery	15%*
c) intracranial abnormality (parenchymal haemorrhage or focal white matter damage) on cranial ultrasound	15%*
d) requirement for supplementary oxygen 28 days after birth	55%*
e) patent ductus arteriosus requiring medical or surgical management	25%*
f) retinal surgery for retinopathy of prematurity	5%*
g) sustained tachycardia (greater than 220 beats per minute for more than 30 minutes in a 60 minute period)	20%**
h) pulmonary haemorrhage	5%**
i) persistent weight loss after 14 days after birth in the absence of infection.	10%**

* based on incidence of these complications at Liverpool Women's Hospital

** based on incidences estimated by the investigators

### Reporting Serious Adverse Events

All expected Serious Adverse Events (SAE) (Table 1) will be recorded in the case report forms (CRF). All deaths or suspected overdoses will be reported using the SAE report forms (See Appendix) to the Chief Investigator (CI) within 24 hours and will be reviewed by the DMEC at regular intervals throughout the trial. The trial sponsor will collate and submit annual safety reports to MHRA and ethics committee. However, the MHRA, the trial sponsor and the chair of the MREC may also be informed about severe adverse events by the DMEC chair if considered appropriate.

A standard reporting procedure will be provided on the reverse side of all SAE forms. A Trial Standard Operating Procedure with detailed information on reporting procedures will also be kept in site files at each 'trial station' in each centre. Copies of all correspondence relating to reporting will be maintained in the Investigator's files.

All adverse events whether or not they are attributable to the study intervention will be reported on case report forms. These will be reviewed by the investigators monthly to determine if there is reasonable suspected causal relationship to the intervention. If there is evidence that there may be a novel causal relationship with the intervention, then the procedure for expedited reporting of suspected unexpected serious adverse reactions will be followed (section 5.4 below). All adverse events will be followed until satisfactory resolution or until the investigator responsible for the care of the participant deems the event to be chronic or the patient to be stable.

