### Suspected Unexpected Serious Adverse Reactions

Given the vulnerability of these infants, the Chief Investigator and the Principal Investigators will review all serious adverse events in order to detect Suspected Unexpected Serious Reactions (SUSARs), involving other members of the Trial Management Group as appropriate. The procedure for identifying and reporting Suspected Unexpected Serious Adverse Reactions will be as follows.

All deaths or overdoses will be reviewed by the Chief Investigator (CI) or in his absence another member of the Trial Management Group. For each death the CI, or his deputy, will make a judgement about whether the nature or severity of the circumstances surrounding the death is consistent with adverse drug reactions associated with levothyroxine. Other members of the Trial Management Group who are available at the time may contribute to a discussion prior to the judgement. The judgement will take place within 24 hours of the notification of a death. If the nature or severity of the events leading up to the death are considered to be related to the study medication but inconsistent with what is known about levothyroxine, the allocation concealment for the affected infant will be broken by the sponsor. In the event of a death occurring in association with events that are not consistent with the information contained in this protocol and the infant was allocated to levothyroxine, the event will be labelled as a Suspected Unexpected Serious Adverse Reaction (SUSAR). If an overdose is thought to have led to a serious adverse event not listed in section 5.2 then the event will be labelled as a SUSAR. All events labelled as SUSARs will be reported to the sponsor within 24 hours of the decision being made. All SUSARs will be reported to the competent regulatory authority (MHRA) with a copy to the Sponsor as soon as possible but not later than 7 working days.

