The Trial Management Group will meet monthly in order to review all other Serious Adverse Events. The Group will consider whether each SAE is consistent with the information contained in this protocol about the nature and severity of adverse drug reactions associated with levothyroxine (including literature cited in the protocol). The CI or his deputy will make a judgement about whether the nature or severity of the circumstances surrounding the death is consistent with the information contained in this protocol about the nature and severity of adverse drug reactions associated with levothyroxine. If the nature or severity of the SAE is judged to be inconsistent with the information contained in this protocol the allocation concealment for the affected infant will be broken. In the event that a SAE occurs in association with events that are not consistent with the information contained in this protocol and the infant was allocated to levothyroxine, the event will be labelled as a Suspected Unexpected Serious Adverse Reaction (SUSAR) and reported as above.

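### Only deaths and suspected overdoses have a stated 24-hour route to the Chief Investigator; an unexpected life-threatening non-fatal event can wait up to a month for its SUSAR judgement

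*Protocol article*

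**What the plan says.** The article's definition of a serious adverse event includes one that "b) is life-threatening", whether or not the infant dies.

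Under Reporting Serious Adverse Events, the expected events of Table 1 are recorded on the case report form. Deaths and overdoses have a faster path: "All deaths or suspected overdoses will be reported using the SAE report forms (See Appendix) to the Chief Investigator (CI) within 24 hours". Adverse events in general go on case report forms, and "These will be reviewed by the investigators monthly to determine if there is reasonable suspected causal relationship to the intervention". If that review points to a possible new causal link, "then the procedure for expedited reporting of suspected unexpected serious adverse reactions will be followed".

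Under Suspected Unexpected Serious Adverse Reactions, the Chief Investigator or a deputy reviews deaths and overdoses. For deaths, "The judgement will take place within 24 hours of the notification of a death". For everything else, "The Trial Management Group will meet monthly in order to review all other Serious Adverse Events". The consistency judgement, the breaking of the allocation and the SUSAR label for these events are described as part of that review. After labelling, "All events labelled as SUSARs will be reported to the sponsor within 24 hours of the decision being made", and the regulator is told within 7 working days. The event that starts those 7 days is not named.

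**The concern.** A SUSAR procedure exists to catch serious reactions that nobody predicted. Here the speed of the route depends on whether the infant died or was overdosed, not on whether the event was unexpected. Death is listed in Table 1 as expected in 20% of infants, yet it gets 24-hour notification and a 24-hour judgement. A life-threatening event of a kind not foreseen gets a monthly review.

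What is at stake is the protection of other infants in the trial. The article says that levothyroxine is rarely used in this population, and that circulating hormone concentrations after dosing have not been studied in it. Siblings from a multiple birth share an allocation, and the intravenous syringes are prepared in a single pharmacy department. A new reaction or a preparation problem could therefore affect further infants while the first case awaits review.

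**Working it through.** There is no planned figure to reproduce. The check follows the stated route and adds up the stated time limits.

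**Inputs from the article**

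| Step | Death | Other non-fatal serious event, no suspected overdose |
|---|---|---|
| Report to Chief Investigator | within 24 hours | no time stated |
| SUSAR judgement | within 24 hours of notification | monthly meeting |
| Report to sponsor | within 24 hours of the decision | same |
| Report to regulator | within 7 working days, start not stated | same |

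**Assumptions**
- Meetings are one calendar month apart, at most 31 days.
- Events fall evenly between meetings.
- The investigators' monthly causality review and the monthly group meeting belong to one cycle and do not run in series.
- Seven working days equal 9 to 11 calendar days, depending on the weekday of the start and ignoring public holidays.

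**Wait before labelling, non-fatal event**
- Maximum: 31 days.
- Mean: 31 / 2 = 15.5, so about 15 days over months of ordinary length.

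**Time to the regulator if the 7 working days start at labelling**
- Non-fatal event, worst case: 31 + 9 = 40 to 31 + 11 = 42 days.
- Death, worst case: 1 (report) + 1 (judgement) + 9 to 11 = 11 to 13 days.

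**If instead the 7 working days start at first awareness, taken as the day of the event**
- The limit expires after 9 to 11 calendar days.
- With a 31-day interval, the share of events whose meeting falls later than that is 1 − 11/31 = 65% to 1 − 9/31 = 71%.
- On this reading the monthly step alone would usually break the limit.

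So either reading of the unstated start causes difficulty. In one, the clock starts only after a wait of up to a month; in the other, the stated review interval cannot reliably meet it.

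**Wording of the non-fatal route.** The paragraph on the monthly meeting describes the judgement as being about the circumstances of the death, although deaths were dealt with in the preceding paragraph. The phrase appears to have been carried over, and it leaves the judgement on non-fatal events poorly defined.

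**The case against.** The strongest reply is that the article is not the whole procedure. It refers to a standard operating procedure in the site files, to instructions on the back of the SAE form and to an appendix. It also cites section numbers that belong to a fuller protocol. Any of these may set a faster notification time. This stands as a limit on what can be said about practice. It does not remove the point, because the article does more than stay silent: it assigns all other serious events to a monthly meeting. A faster rule elsewhere would conflict with that.

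Second, the SUSAR section opens by saying that the Chief Investigator and Principal Investigators review all serious adverse events. That review has no time limit, and the procedure introduced straight afterwards sets the monthly interval. The power of the monitoring committee's chair to inform the regulator is discretionary and untimed, and the emergency committee meeting is triggered by a rise in expected events.

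Third, other contacts could bring the Chief Investigator in early. Emergency unblinding, for example, is to be discussed with that role first. This is fair. A reader might infer that the Chief Investigator cannot hear of such an event before the meeting, or that the SAE form may not be used for it. The article says neither; it only gives no time by which notification must happen.

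Fourth, a monthly detection step before expedited reporting is slow, but it is not a logical contradiction, since the expedited procedure is defined as what follows suspicion. That also stands.

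**Conclusion.** The point holds as a weakness in the stated procedure. A serious event that is neither fatal nor a suspected overdose has no stated time for reaching the Chief Investigator, and its SUSAR judgement is tied to a monthly meeting. The delay before labelling is up to about 31 days, with a mean of about 15, assuming meetings a calendar month apart.

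The 40 to 42 days to the regulator is a worst case. It also assumes that the 7-working-day limit starts at labelling. A reader might take that start as given, but the article ties only the 24-hour report to the sponsor to the decision.

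A reader might also infer that the delay covers a whole treatment course. From birth to 32 weeks is 29 days for an infant born at 27+6 (224 − 195) and 56 days for one born at 24+0 (224 − 168), so this is not true in general. The affected infant's course is in any case the wrong yardstick, because treatment of that infant may be discontinued under Subject Withdrawal. The exposure that matters is that of other infants, and the article gives no basis for quantifying it.

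The text should be changed. Confidence is moderate because the operating procedure is not shown.

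**What to change.** In Reporting Serious Adverse Events, add a third class to the 24-hour route, for example:

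> Deaths, suspected overdoses, and any serious adverse event that the site investigator suspects is related to study drug and that is either absent from Table 1 or of unexpected nature or severity, are notified to the Chief Investigator on the SAE form within 24 hours.

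Then:
- apply the 24-hour judgement already set for deaths to this class;
- state that the 7-working-day limit to the regulator runs from first awareness of the event;
- keep the monthly meeting for the remaining serious events;
- remove the reference to a death from the paragraph on non-fatal events;
- check the standard operating procedure and the SAE form instructions against the revised text.

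Absence from Table 1 should not be the only trigger. It would miss a listed event of unusual severity. It would also sweep in unlisted events with no suspected link to the drug, since any event that prolongs hospitalisation counts as serious.

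The cost is a short amendment that uses an existing form and existing roles, plus some additional SAE forms and ad hoc reviews by the Chief Investigator. The requirement that the event be both suspected as related and unexpected limits that load. The documents give no figure from which to estimate it.

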### Suspected Unexpected Serious Adverse Reactions

Given the vulnerability of these infants, the Chief Investigator and the Principal Investigators will review all serious adverse events in order to detect Suspected Unexpected Serious Reactions (SUSARs), involving other members of the Trial Management Group as appropriate. The procedure for identifying and reporting Suspected Unexpected Serious Adverse Reactions will be as follows.

All deaths or overdoses will be reviewed by the Chief Investigator (CI) or in his absence another member of the Trial Management Group. For each death the CI, or his deputy, will make a judgement about whether the nature or severity of the circumstances surrounding the death is consistent with adverse drug reactions associated with levothyroxine. Other members of the Trial Management Group who are available at the time may contribute to a discussion prior to the judgement. The judgement will take place within 24 hours of the notification of a death. If the nature or severity of the events leading up to the death are considered to be related to the study medication but inconsistent with what is known about levothyroxine, the allocation concealment for the affected infant will be broken by the sponsor. In the event of a death occurring in association with events that are not consistent with the information contained in this protocol and the infant was allocated to levothyroxine, the event will be labelled as a Suspected Unexpected Serious Adverse Reaction (SUSAR). If an overdose is thought to have led to a serious adverse event not listed in section 5.2 then the event will be labelled as a SUSAR. All events labelled as SUSARs will be reported to the sponsor within 24 hours of the decision being made. All SUSARs will be reported to the competent regulatory authority (MHRA) with a copy to the Sponsor as soon as possible but not later than 7 working days.

The Trial Management Group will meet monthly in order to review all other Serious Adverse Events. The Group will consider whether each SAE is consistent with the information contained in this protocol about the nature and severity of adverse drug reactions associated with levothyroxine (including literature cited in the protocol). The CI or his deputy will make a judgement about whether the nature or severity of the circumstances surrounding the death is consistent with the information contained in this protocol about the nature and severity of adverse drug reactions associated with levothyroxine. If the nature or severity of the SAE is judged to be inconsistent with the information contained in this protocol the allocation concealment for the affected infant will be broken. In the event that a SAE occurs in association with events that are not consistent with the information contained in this protocol and the infant was allocated to levothyroxine, the event will be labelled as a Suspected Unexpected Serious Adverse Reaction (SUSAR) and reported as above.

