### Possible negative effects of giving T4

Thyroxine is infrequently given to extremely premature babies. The only adverse effect that might be predicted is based on clinical experience of giving the drug to more mature patients, namely a persistent tachycardia. The drug may increase metabolic rate. In the critical paper by van Wassanaer et al[8], there was no difference in neurodevelopmental outcome as a result of T4 supplementation. However, a *post hoc *subgroup analysis showed that more mature babies who were given T4 supplementation had a worse neurodevelopmental outcome than those who were unsupplemented. The mechanism for this possible effect is not known.

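### The overdose rule for SUSARs tests expectedness against the list of prematurity complications and has no allocation check, unlike the rules for deaths and for other serious events

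*Protocol article*

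**What the plan says.** The section Suspected Unexpected Serious Adverse Reactions of the protocol article contains three labelling rules.

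- **Deaths.** The Chief Investigator or a deputy judges each death. If the events leading to it are "considered to be related to the study medication but inconsistent with what is known about levothyroxine", the sponsor breaks the allocation. The SUSAR label applies if the events "are not consistent with the information contained in this protocol and the infant was allocated to levothyroxine".
- **Overdoses.** "If an overdose is thought to have led to a serious adverse event not listed in section 5.2 then the event will be labelled". The label in question is SUSAR, and the sentence says nothing more about expectedness or allocation.
- **Remaining SAEs.** The Trial Management Group reviews these monthly against the protocol's information, and its cited literature, on the nature and severity of adverse reactions to levothyroxine. If an event does not fit, allocation is broken, and the label depends on the infant having been allocated to levothyroxine.

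Table 1, under Expected Serious Adverse Events, is introduced as "serious adverse events and incidence rates which could be reasonably expected for this group of babies during the course of the study". Its rates come from one hospital's experience or from the investigators' estimates.

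**The concern.** A SUSAR is a suspected reaction that is unexpected for the drug. The overdose sentence already supposes that the overdose caused the event. What remains to be asked is whether levothyroxine is known to do this, in this form and to this degree. The sentence asks instead whether the event is common in extremely premature infants. A complication can be common in that population and still be an unexpected result of too much levothyroxine.

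At stake is the consistency of expedited reporting to the regulator. A harm attributed to an overdose meets a less relevant test than the same harm at the intended dose, and a placebo event can be reported as a SUSAR.

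**Working it through.** No figure in the plan depends on this point, so the check compares the rules.

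**Step 1: what section 5.2 is.** The article carries no section numbers. Under Adverse Event Reporting and Safety Evaluations the subsections run: Definitions, Expected Serious Adverse Events, Reporting Serious Adverse Events, Suspected Unexpected Serious Adverse Reactions. The reporting subsection refers to the SUSAR procedure as section 5.4. Counting back, 5.2 is Expected Serious Adverse Events, that is, Table 1.

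**Step 2: the three rules side by side.**

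| Rule | Reference for expectedness | Allocation broken first | Label requires levothyroxine |
|---|---|---|---|
| Death | What is known about levothyroxine | Yes | Yes |
| Overdose | Table 1 (population complications) | Not stated | Not stated |
| Remaining SAEs | Protocol's information on reactions to levothyroxine | Yes | Yes |

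**Step 3: how far Table 1 and drug knowledge differ.** Table 1 has nine items.

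- Death has its own rule, which leaves 9 − 1 = 8.
- Sustained tachycardia is listed ("g) sustained tachycardia (greater than 220 beats per minute for more than 30 minutes in a 60 minute period") and is also the drug's predicted effect: "The only adverse effect that might be predicted is based on clinical experience of giving the drug to more mature patients, namely a persistent tachycardia". Both references agree on its nature, though severity could still differ. That leaves 8 − 1 = 7.
- Persistent weight loss is arguable, because the article says that the drug may raise metabolic rate and could reduce growth. That leaves 7 − 1 = 6.
- The other six are necrotising enterocolitis or focal intestinal perforation, intracranial abnormality, oxygen requirement at 28 days, patent ductus arteriosus needing management, retinal surgery, and pulmonary haemorrhage. The article describes none of them as an effect of levothyroxine.

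**Step 4: two cases through the rules.**

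*Non-fatal pulmonary haemorrhage, levothyroxine arm, attributed to study drug.* Without an overdose, the rule for remaining SAEs applies. The event does not match the article's description of levothyroxine reactions, so allocation can be broken and the event labelled. With an overdose thought to be the cause, the overdose sentence does not label it, because it is in Table 1. The monthly review covers what is left after deaths and overdoses have been dealt with, so it can be read as not reaching this case.

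*Unlisted serious event after an overdose of placebo, thought to be caused by it.* The overdose sentence labels it a SUSAR. Under either neighbouring rule the allocation would be broken and the label withheld.

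**The case against.** The strongest reply is that the overdose sentence is one trigger among several. It says that an unlisted event will be labelled if attributed to an overdose, not that only such events will be. The section opens with investigator review of all SAEs to detect SUSARs, and the reporting section sends any suspected novel causal relationship to expedited reporting. Every suspected overdose goes to the Chief Investigator within 24 hours and is reviewed by the DMEC. The missing allocation condition errs towards over-reporting, and labelled events go to the sponsor, which can break the allocation. A standard operating procedure with more reporting detail exists but is not shown.

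Much of this stands, and it rules out three stronger readings.

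- A reader might infer that fatal overdoses escape because death and tachycardia are in Table 1. They do not. The death rule covers every death, has no Table 1 exemption and considers severity as well as nature. Since the article treats tachycardia as a relatively trivial effect (Ethical issues), a fatal one could be judged inconsistent with what is known.
- A reader might infer that the DMEC is kept uninformed. The 24-hour report and regular DMEC review apply to all suspected overdoses.
- A reader might add up the Table 1 incidences (20+15+15+55+25+5+20+5+10 = 170%) and conclude that most overdose events are exempt. Those are background rates over the whole study. They do not measure events caused by overdoses, and no overdose rate is given.

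The reply does not remove the mismatch. The opening review of all SAEs is carried out through the procedure that follows it, which includes the overdose sentence. The novel-relationship route leads back to the same section. The 24-hour report goes to the Chief Investigator, not to the regulator. And this is a stated rule that conflicts with its neighbours, not a detail left to a fuller document.

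**Conclusion.** The point holds in a limited form. The overdose sentence uses a different reference for expectedness from the two adjacent rules and omits their allocation condition. Two kinds of event are affected: non-fatal Table 1 events attributed to an overdose, most clearly the six items not described as drug effects, and unlisted events attributed to a placebo overdose.

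The conclusion rests on two readings: that section 5.2 is Table 1, which the cross-references make very probable, and that the protocol information used in the review of remaining SAEs means its information on levothyroxine reactions, as that paragraph's fuller wording says, and not Table 1. Whether the monthly review excludes overdose cases is open to interpretation. The number of events affected cannot be calculated from the document. The consequence is inconsistent expedited reporting; the trial's efficacy analysis is not touched.

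**What to change.** Reconcile the overdose sentence with the rules on either side of it. This changes safety-reporting wording only.

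1. Replace the reference to section 5.2 with the test used for deaths and remaining SAEs: is the nature or severity of the event consistent with the protocol's information on adverse reactions to levothyroxine?
2. Add the same allocation step: break the allocation when the event is judged inconsistent, and apply the SUSAR label only if the infant was allocated to levothyroxine.

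The cost is a wording change to the protocol and the matching change to the reporting procedure, with possibly a few more expedited assessments and sponsor unblindings.
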